### Current status

The RAMIE trial has been ethically approved by the ethics committees of Shanghai Chest Hospital (KS1734). Recruitment of patients was started in July 1st, 2017. It is still at the stage of recruiting as 210 patients have been recruited until December 1st, 2018.

## Discussion

Minimally invasive esophagectomy, including MIE and RAE, have been used to reduce postoperative complication and improve postoperative recovery compared with open esophagectomy. Theoretically, RAE seems to get better short-term and oncological results, which could be supported by the facilitated manipulation and precise dissection of robotic system [26]. However, controversy still exists on the potential advantages of RAE versus MIE. To the best of our knowledge, this is the first randomized controlled trial designed to compare RAE with MIE as surgical treatment for patients with resectable ESCC.

Surgical resection with radical lymphadenectomy remains a critical element in the treatment of esophageal cancer. Therefore, the majority of studies concerning the application of RAE and MIE have focused on the extent of lymphadenectomy, especially for mediastinal lymph node dissection. Several retrospective studies demonstrated that RAE yielded significantly more lymph nodes than MIE especially in the upper mediastinum [19, 27, 28]. Lymph nodes dissection along the bilateral recurrent laryngeal nerve (RLN) is key step due to its high metastatic rate, but it is technically challenging because of narrow operative space. The feasibility and safety of the robot-assisted lymphadenectomy along the bilateral RLNs were demonstrated in a previous study [29]. Chao et al. also showed that compared with MIE, RAE resulted in a higher lymph node yield along the left RLN without increasing morbidity [28]. Thoracoscopic instruments have their limitations with respect to dissection in a small and narrow space. Instead, robotic surgery has several technological advantages as it provides a three-dimensional view, ten times magnification, tremor control, and ambidexterity.

The advantage of robotic system gives surgeons greater confidence of achieving a complete bilateral RLN lymph nodes dissection, but this may increase the incidence of postoperative RLN injury. Studies show the postoperative RLN injury rate range from 9.1 to 20.6% in RAE group as from 3.8 to 29.4% in MIE group, there is no significant difference between the two groups [19, 27, 28, 30]. The left RLN injury is more common than the right RLN. Notably, RLN injury can be caused by contusions, excessive stretching, and thermal damage occurring during manipulation. Chao et al. reported their method reducing the RLN injury by using the third robot arm (controlled by the operator) which allows achieving an excellent operating exposure through the application of stable and self-controllable tractions and countertractions on the esophagus and trachea [28].

Since robotic surgery has just begun to be accepted by thoracic surgeon, several groups show that the operation time of robot-assist esophagectomy is significantly higher than that of thoracoscopic esophagectomy, especially one-lung ventilation time [19, 30]. This has the potential to increase postoperative respiratory complications, but no significant increase in the risk of respiratory complications was identified in the RAE group. These studies also have found that no significant increase in the risk of anastomotic leakage, or other postoperative complication. For the reason that the surgeon can perform complex procedures sitting comfortably, they have not felt fatigued even if the prolong of operative time.

Although RAE is reported to improve the efficiency of lymph node dissection, it is unclear whether more extensive lymph node dissection could result in a significant survival advantage. Fewer studies were designed to focus on comparing long-term survival between RAE and MIE. Park et al. reported that the 5-year overall survivals were not different between the two groups (69% in RAE vs. 59% in MIE, *P* = 0.737). The 5-year freedom from locoregional recurrence was 88% in the RAE group and 74% in the MIE group, however the difference was not statistically significant (*P* = 0.100, 19]. The primary endpoint of our controlled trial is 5-year overall survival. According to our hypothesis, RAE will result in at least similar oncological outcomes and long-term quality of life compared with MIE.

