**Methods:**

This study is designed as a multicenter, prospective, randomized, non-inferiority phase III clinical trial, investigating the safety and efficacy of RAE compared with MIE in the treatment of resectable ESCC. Eligible patients are randomly assigned to either RAE (*n* = 180) or MIE (*n* = 180) group. The follow-up visits will be scheduled at 3, 6, 9, and 12 months in the first two years, and then every 6 months until the end of the study. During the follow-up period, clinical data and quality of life questionnaires will be examined. The primary endpoint is the 5-year overall survival (OS). The secondary endpoints are 3-year OS, 5-year disease-free survival (DFS), short-term outcomes as well as quality of life.

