**Discussion:**

This is the first prospectively randomized controlled trial designed to compare RAE with MIE as surgical treatment for resectable ESCC. According to our hypothesis, RAE will result in at least similar oncologic outcomes and long-term quality of life, but with a shorter operation time, lower percentage of perioperative complications, lower blood loss, and shorter hospital stay when compared with MIE. This study started in July 2017. Follow-up will terminate after 5 years from the time when the last patient was enrolled.

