### Sample size considerations

The sample size was calculated based on the primary outcome overall survival. A non-inferiority trial is planned in which the primary analysis will use the non-inferiority log-rank test. Generally, non-inferiority margins in local-advanced cancers were in a narrow range (1.18–1.33) according to the FDA’s estimate [21]. After extensive discussion, the researchers have decided that the upper bound on non-inferiority is 1.33. The total trial will take about 7 years which consists of 2-year recruitment period and 5-year follow-up period. We estimated a missing rate of 5% per year in each group. A hazard rate of 0.60, a power of 0.80 and a significance level of 0.05 will be used. Based on the assumptions, a sample size of 360 (2 × 180) participants was calculated using PASS 11 software (NCSS, LLC; Version 11.0.7).

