### Statistical analysis

Statistical analyses are performed using SPSS version 20.0 software (SPSS Inc. Chicago, Illinois, USA). Survival will be estimated by Kaplan-Meier methods and analyzed using log-rank test. Complications will be calculated as percentage with 95% confidence intervals and analyzed by χ^2^ test or Fisher’s exact test. Student’s *t* test and analysis of variance (ANOVA) test was conducted for the comparison in continuous variables, while χ^2^ test or Fisher’s exact test was used in categorical variables. *P* < 0.05 is set as the significance level.

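### Long-term quality of life is hypothesised to be at least similar, but the stated analysis has no margin for it and only a test of difference

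*Protocol article*

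**What the plan says.** The hypothesis on QOL appears twice. The abstract expects that "RAE will result in at least similar oncologic outcomes and long-term quality of life", and the main Discussion closes with "RAE will result in at least similar oncological outcomes and long-term quality of life compared with MIE". QOL is a named secondary endpoint, measured with QLQ-C30 and QLQ-OES18 from randomisation until 3 years after surgery (Secondary endpoints).

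The only margin is in Sample size considerations, for overall survival: "the researchers have decided that the upper bound on non-inferiority is 1.33". That section also names a non-inferiority log-rank test for the primary analysis.

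Statistical analysis does not mention QOL by name. For scores of this kind it offers Student's t test and "analysis of variance (ANOVA) test was conducted for the comparison in continuous variables", at P<0.05. On complications it says "Complications will be calculated as percentage with 95% confidence intervals and analyzed by" chi-square or Fisher's exact test.

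The short-term hypothesis points the other way. The abstract expects RAE to match MIE on oncologic outcomes and QOL, "but with a shorter operation time, lower percentage of perioperative complications, lower blood loss, and shorter hospital stay when compared with MIE". On RLN injury, the Discussion says of the more complete robotic dissection that "this may increase the incidence of postoperative RLN injury".

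**The concern.** A claim that one arm is at least similar to the other needs a limit on how much worse it may be, and an interval that excludes anything beyond that limit. The article does this for survival and not for QOL, although it states the two in the same sentence. A t test at P<0.05 can show that RAE is better or that it is worse. When it shows neither, it does not separate a close match from too little information.

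This matters most for late QOL, because deaths and loss to follow-up reduce the numbers by 3 years. If a non-significant result were taken as support, the claim would become easier to make as fewer patients were assessed.

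RLN injury raises a related, smaller point. It is the harm that the article itself singles out, and the planned 95% CIs are attached to complication percentages. None is stated for the difference between arms.

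**Working it through.** **No plan figure to reproduce.** The article gives no sample size, power, SD or relevant difference for QOL or RLN injury. The 360 was calculated for overall survival and enters here only as 180 per arm.

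**Inputs.**
- 180 per arm and 5% loss per year: Sample size considerations.
- 5-year survival of 25% (top of the 15–25% range in Background), 59% and 69% (MIE and RAE in the cohort cited in the Discussion).
- Last QOL assessment at 3 years: Secondary endpoints.
- Assumptions: exponential survival, the same in both arms; every remaining survivor completes the questionnaire; deficits in SD units, because no SD is given; two-sided 0.05.

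**Patients per arm at 3 years.** n = 180 × S(3) × 0.95³, with S(3) = S(5)^(3/5) and 0.95³ = 0.857.
- 25%: S(3) = 0.435, n = 67
- 59%: S(3) = 0.729, n = 112
- 69%: S(3) = 0.800, n = 123

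**Chance that the t test misses a true QOL deficit** (noncentral t, noncentrality d√(n/2)), **and chance of meeting a 0.5-SD margin** when the arms are truly equal, Φ(0.5√(n/2) − 1.96):

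| 5-year survival | n per arm | 0.3 SD missed | 0.5 SD missed | 0.5-SD margin met |
|---|---|---|---|---|
| 25% | 67 | 59% | 18% | 83% |
| 59% | 112 | 39% | 4% | 96% |
| 69% | 123 | 35% | 2.5% | 98% |

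The half-width of the 95% CI for the mean difference, 1.96√(2/n), is 0.34, 0.26 and 0.25 SD in the three rows. A non-significant result is therefore compatible with a true deficit larger than 0.3 SD, since the observed difference may itself lie below zero.

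**RLN injury, 180 per arm.** The chi-square test misses a true rise from 10% to 20% with probability 23%, from 15% to 25% 33%, and from 20% to 30% 40% (exact binomial enumeration, no continuity correction). These rates are assumed, chosen within or near the ranges cited in the Discussion (9.1–20.6% RAE, 3.8–29.4% MIE). With equal true rates p, the half-width of the 95% CI for the risk difference is 1.96√(2p(1−p)/180): 6.2 points at 10%, 8.3 at 20% and 9.4 at 29.4%.

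**The case against.** The strongest reply is that this is a secondary endpoint in a condensed article. Scale, time point and margin often sit in the full protocol or analysis plan, which is not shown. Statistical analysis is a short list that does not name QOL or repeat the non-inferiority survival test, so assigning t test/ANOVA to QOL is an inference, though a natural one. This limits the finding but does not remove it. The article states both a hypothesis and a set of tests, and the tests cannot establish the hypothesis. It also shows with survival that a margin was available as a tool.

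Second, a reader might infer that safety is also claimed to be at least similar. The documents do not support this. The hypothesis for complications is a lower percentage, which a difference test fits and which low power works against. The abstract's "investigating the safety and efficacy of RAE compared with MIE in the treatment of resectable ESCC" states an aim, and no sentence says that this trial will show similar RLN injury.

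Third, a reader might infer a rule that P>0.05 means similar. No such rule is written. The Discussion does treat non-significant results in earlier studies as no difference (for example 69% vs 59% survival), but that is a literature summary. It shows a risk of misreading and does not amount to a plan.

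Fourth, more alarming figures can be produced and should not carry the point. Reading the planning hazard of 0.60 as yearly leaves about 25 per arm at 3 years and a 58% chance of missing 0.5 SD. It also implies about 5% survival at 5 years (e^−3), against the 15–25% and 59–69% cited elsewhere, so it belongs to a sample-size question. Setting 3.8% (MIE) against 9.1% (RAE) for RLN injury pairs the lower ends of two ranges. The upper ends (29.4% vs 20.6%) favour RAE, and neither pair is shown to come from one study.

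Finally, a 0.5-SD deficit would usually be detected under the survival range used, which keeps the size of the problem moderate.

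**Conclusion.** The point holds for QOL. The article makes a non-inferiority claim on long-term QOL and pairs it with difference tests and no margin, so unless RAE is shown to be better the stated analysis cannot support the claim. At 3 years a 0.3-SD deficit would go undetected in 35% to 59% of trials and a 0.5-SD deficit in 2.5% to 18%. These figures rest on 5-year survival of 69% down to 25%, 5% yearly loss and full questionnaire return among survivors. Lower survival or poorer return would worsen them.

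For RLN injury only the narrower point stands: a harm that the article anticipates should be reported as a between-arm difference with its interval, and its absence should not be read from P>0.05. There is no basis for saying that the safety analysis as a whole is of the wrong type. The primary survival comparison is not touched by this point.

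**What to change.** In Statistical analysis:

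1. **QOL.** State that at least similar QOL will be concluded only if the 95% CI for the RAE–MIE mean difference on one named scale and time point (for example QLQ-C30 global health status at 36 months) excludes a worsening beyond a margin that the sponsor fixes now. Otherwise report the result as inconclusive. As an illustration, 0.5 SD would be met 83% to 98% of the time if the arms are truly equal. If no margin can be justified, reword the QOL hypothesis as descriptive in the abstract and the Discussion.
2. **RLN injury/vocal cord palsy.** Report the RAE–MIE risk difference with its 95% CI beside the planned percentages, and state that absence of harm will not be inferred from P>0.05. A formal margin is not needed and could be hard to meet: by Φ(0.10/√(2p(1−p)/180) − 1.96), a 10-point margin would be met about 88% of the time at a 10% rate in both arms, but about 66% at 20%.
3. **Keep the existing tests** for the superiority hypotheses, including fewer complications.

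The cost is some analysis wording and a few confidence intervals, with no new patients or data. The downside is that some results may have to be reported as inconclusive.

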## Data Availability

This article has used no dataset. Therefore, no additional data files are available.

## Abbreviations

AJCC: American Joint Committee on Cancer
CT: Computed tomography
DFS: Disease-free survival
ECCG: Esophagectomy Complications Consensus Group
ECOG: European Clinical Oncology Group
EORTC: European Organization for Research and Treatment of Cancer
ESCC: Esophageal squamous cell carcinoma
MDT: Multidisciplinary team
OS: Overall survival
OTE: Open transthoracic esophagectomy
PET-CT: positron emission tomography-computed tomography
QOL: Quality of life
RAE: Robot-assisted esophagectomy
RAMIE: Robot-Assisted Minimally Invasive Esophagectomy
RLN: Recurrent laryngeal nerve
UICC: International Union for Cancer Control
